### Sample size calculation

Power analysis using procedures appropriate for a cluster RCT study design [51] were conducted to determine the sample size required to detect changes in the primary outcome of accelerometer-determined physical activity counts per minute (CPM). Calculations assumed baseline to post-test correlation scores of *r* = 0.30 and were based on 80% power and alpha level 0.05. Based on the reported physical activity effects (i.e., *SD* change = 200 CPM) after six weeks of the TWM in Maths study pilot study, and a conservative intra-class correlation coefficient (ICC = 0.15), a study sample of *N* = 200 with 8 clusters (i.e., schools) of 25 students would provide adequate power to detect a between group difference of 200 CPM across the school day [34, 52].

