### Statistical analyses

Primary and secondary outcomes will be analyzed through linear mixed models, as they are robust to the biases of missing data and provide appropriate balance of Type 1 and Type 2 errors [77, 78]. Taking into account the hierarchical structure of the data in educational research (e.g., students nested within classes and schools), multilevel modelling analyses can be linked to several predictor variables at the individual level (e.g., students) and at a group levels (e.g., classrooms, schools [79, 80]). In this study, the models will be specified to adjust for the clustered nature of the data (i.e., class level was included as a random intercept) including all randomized participants in the analysis. Previous studies have shown that school-level clustering is negligible after accounting for clustering at the class level [81]. Analyses will be conducted using SPSS (version 22) and alpha levels will be set at *p* > 0.05. Data will be analyzed according to intention-to-treat principles. Qualitative data from teachers and students semi-structured interviews will be processed using a standard general inductive approach to qualitative analysis [82, 83]. Data will be transcribed verbatim, and then will be coded using thematic analysis.

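### The analysis section prints the significance threshold as p > 0.05, the reverse of the alpha of 0.05 used for the sample size: a minor slip, but in the only decision rule stated

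*Protocol article*

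**What the plan says.** The Statistical analyses section says that primary and secondary outcomes will be analysed with linear mixed models. For the threshold at which a result counts as significant, it says only that "alpha levels will be set at *p* > 0.05". The sentence does not separate the primary from the secondary outcomes, so it governs both.

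The one other place that gives an error rate is the Sample size calculation section, where the calculations "were based on 80% power and alpha level 0.05". No other section states a significance threshold, and none corrects the sign.

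**The concern.** An alpha level is the probability of rejecting a true null hypothesis. With alpha at 0.05, the null is rejected when p is below 0.05. The analysis section attaches the opposite inequality to the same number, so the printed rule counts as significant the results that the sample size section treats as non-significant, and the reverse.

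What is at stake is the internal consistency of the plan. The sentence is the trial's stated rule for claiming an effect on physical activity, on-task behaviour, academic achievement and executive function. A reader who later compares the results paper with the protocol should find a rule that can be applied as printed.

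**Working it through.** **Step 1: the two statements side by side.**

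- Sample size calculation: alpha 0.05, so an effect is declared if p < 0.05.
- Statistical analyses: an effect is declared if p > 0.05.

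The number is the same and the inequality is opposite. If one statement is right, the other is wrong.

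**Step 2: what each rule implies when there is no effect.** For a valid test with a continuous statistic, p is uniform on 0 to 1 under the null.

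- P(p < 0.05) = 0.05, which equals the alpha in the sample size section.
- P(p > 0.05) = 1 − 0.05 = 0.95, which does not.

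**Step 3: does the plan's own sample size rest on the ordinary rule?** Inputs, all from the Sample size calculation section:

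- correlation: "Calculations assumed baseline to post-test correlation scores of *r* = 0.30"
- standard deviation: "SD* change = 200 CPM"
- "a conservative intra-class correlation coefficient (ICC = 0.15"
- "a study sample of *N* = 200 with 8 clusters (i.e., schools) of 25 students"
- the claim that this sample "would provide adequate power to detect a between group difference of 200 CPM across the school day"

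The design effect is 1 + (25 − 1) × 0.15 = 4.6. With 100 pupils per arm, the effective number per arm is 100 / 4.6 = 21.74.

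The variant closest to the stated N under a normal approximation treats 200 CPM as a cross-sectional SD. This is an assumption, since the text labels the figure as an SD of change. The change-score SD is then 200 × √(2 × (1 − 0.30)) = 236.6.

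- Required per arm at two-sided 0.05 and 80% power: 2 × (236.6 × (1.960 + 0.842) / 200)² × 4.6, which rounds up to 102. The total is 204, against the stated 200.
- Power at N = 200: the standard error is 236.6 × √(2 / 21.74) = 71.8, and 200 / 71.8 = 2.79. Power is Φ(2.79 − 1.96) = 79.6%.

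So the ordinary rule at 0.05 gives the stated sample size to within 2%.

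**Step 4: the printed rule applied to the same calculation.** The chance of declaring the planned 200 CPM difference would be 1 − 0.796 = 20.4%. With 200 CPM taken as the SD of change, as labelled, power under the ordinary rule is 90.9%, and the printed rule would give 1 − 0.909 = 9.1%. Neither is compatible with a calculation that aims at 80% power. The printed inequality is therefore the one that has to change.

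**Step 5: could this be a fault of text extraction?** Both inequality signs come through legibly elsewhere in the article: in the valid-day criterion under Physical activity and in the accuracy rule under Executive function. Nothing suggests a general conversion fault.

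**The case against.** The strongest answer is that nobody will be misled. The term alpha level already carries its meaning, the sample size section states 0.05 with 80% power, and together they leave one workable reading, p < 0.05. On this view it is a one-character slip that alters no analysis, no sample size and no conclusion. All of that stands, and it is why the point is minor. It does not make the printed rule correct.

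Three stronger readings are tempting, and the documents do not support them.

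- **That the trial would declare effects for 95% of true nulls.** A reader might infer this from the literal text. It would require analysts to apply the rule as printed, against the alpha in the sample size section, and nothing suggests that they would.
- **That the silence on one- or two-sided tests is part of the error, or that the sample size proves a two-sided test.** The hypothesis under Aims and hypotheses is directional, so a reader might suspect room for a one-sided test. But no passage proposes one, and sidedness is commonly left to an analysis plan, which is not shown here. Nor does the sample size settle it. With 8 schools and t on 6 degrees of freedom, SD 236.6 one-sided gives 79.1% power and SD 200 two-sided gives 78.4%. Both are close to the 79.6% from SD 236.6 two-sided with a normal approximation.
- **That secondary outcomes should be reported only as estimates with confidence intervals.** This is a reporting preference and does not follow from a reversed sign.

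**Conclusion.** The threshold is wrong as written and contradicts the plan's own alpha. The contradiction is plain from the two sentences and needs no assumption beyond the usual meaning of alpha. Reading it as a slip for p < 0.05 rests on the sample size section, which makes sense only with the ordinary rule.

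Severity is minor. With the sign corrected, the type I error is 0.05, as the sample size section has it, and the design and N = 200 are untouched. The figures of 95% and 20.4% (9.1% if 200 CPM is the SD of change) describe the literal text, not an expected outcome. The uncertainty over how the 200 CPM standard deviation is meant is a separate matter and has no bearing on this conclusion.

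**What to change.** In the Statistical analyses section, replace the phrase with: *statistical significance will be set at p < 0.05*. This matches the alpha in the Sample size calculation section. The cost is one phrase in the article, or a short correction notice. Nothing in the design, data collection, sample size or model needs to change.

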## Discussion

The primary aim of this study is to assess the impact of a curriculum-based physical activity intervention program, integrating physical activity into English lessons, on children’s physical activity levels. The secondary aims are to examine the impact of the program on children’s on-task behavior, academic achievement in English and executive function. The program will be delivered by classroom teachers, after receiving 1-day professional learning workshop. Previous intervention programs that integrate physical activity during learning have been shown to increase physical activity levels and are perceived as the preferred instructional method by children [28, 30–32, 34, 35, 43].

In addition, these programs have found positive effects on children’s academic achievement (e.g., language [26, 29, 33, 84, 85]). Using task-relevant movements which can be translated into academic concepts is suggested to be an effective way of learning due to the mental connection of the physical with the cognitive task [32]. Likewise, physical activity interventions have been proven to foster executive function skills in children [36, 86, 87]. Specifically, cognitively enriched physical activity programs, including chronic physical activity with cognitive training, have found improvements in primary school children’s shifting performance [38, 88], inhibition and updating [86]. Inhibition and shifting were also improved in adolescents through acute effects of exercise (i.e., single bouts [36, 89]).

Lastly, the current physical activity intervention emphasizes the significant role of the teacher on intervention outcomes [90]. The provision of high-quality professional learning development to teachers is necessary for promoting fundamental changes to occur in children’s physical activity [91, 92]. Giving flexibility to teachers to design and develop their learning lessons based on a movement-based curriculum will possibly increase sustainability of the program and allow teachers to integrate it across other grades and curriculum areas.

The cluster RCT design is a significant strength of this study, including quantitative and qualitative measures to explore the program feasibility. In addition, the program was designed based on previous successful studies [34, 43]. The protocol of the study includes detailed process evaluations taking into account students’ and teachers’ point of views. Identifying strengths, but also challenges and barriers, will ensure that the physical activity programs combined with academic instruction are addressing students’ and teachers’ needs with the perspective of a longer-term implementation even after the end of the intervention duration. Such programs, including stealth interventions, are considered the most effective way to foster physical activity [93].

Concluding, the current study may provide time-constrained solution for schools focusing on the dual goal of increasing physical activity and academic achievement. The suggested instructional approach of TWM-E allows educators to decide how to implement these activities in the classroom based on shared quidelines. This flexible implementation increases the likelihood that the program will be adopted by other teachers, overcoming existing barriers, and promoting the dissemination of this study in primary schools across Australia. The partnership with the NSW Department of Education School Sport Unit increases the sustainability of this program in the long-run.

## Abbreviations

CONSORT: Consolidation standards of reporting trials
CPM: Counts per minute
ICSEA: Index of community socio-educational advantage
MVPA: Moderate-to-vigorous physical activity
NAPLAN: National assessment program for literacy and numeracy
NIH: National Institute of Health
NSW: New South Wales
PAT: Progressive achievement test
PDHPE: Personal development, health, and physical education
RCT: Randomized controlled trial
SPSS: Statistical package for social sciences
TWM: Thinking while Moving
TWM-E: Thinking while Moving in English
